### Secondary outcomes

3.2

Quality of life: Patients will be submitted to anamnesis for knowledge of their general clinical picture and history of oral health, as well as intraoral clinical examination and evaluation of drugs used to control hypertension. All subjects will complete a questionnaire (OHIP 14) on quality of life and xerostomia, as well as an analysis of lip and oral mucosa dehydration.

Biochemical analysis: Analysis of salivary total proteins, urea, and calcium levels was quantified in triplicates using colorimetric analysis with commercially available kits (Bioclin, Belo Horizonte, Minas Gerais, Brazil) and a spectrophotometer (Anthos 2020—Asys - Austria). The absorbance for each marker was measured using the wavelength indicated by manufacture.

### Statistical analyzes

3.3

The data will be analyzed regarding its distribution using the Shapiro-Wilkins test and then submitted to the appropriate tests to determine the differences between the groups. If the outcome presents data with normal distribution, the *t* test will be used. If the outcome does not present normal data, the Mann–Whitney *U* test will be used. All tests will be 2-tailed and the level of significance adopted will be *α* = 0.05.

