**Methods::**

This is a randomized, placebo-controlled, blind clinical protocol that aims to analyze the impact of phobiomodulation (PBM) on salivary glands of patients with antihypertensive drug induced xerostomia. Patients will be divided into 2 groups: G1: older adults with xerostomia induced by antihypertensive drugs and treatment with PBM (n = 30); G2: placebo PBM (n = 30). The irradiation will be made using a diode laser emitting at 808 nm with 100 mW and 40 seconds of exposure per site at the salivary glands. Twenty sites will be irradiated weekly for 4 weeks. Non-stimulated and stimulated salivary flow will be analyzed before and after the treatment.

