**Figure 3 F3:**
[figure not shown]
Statistical power of the hypothesis test as a function of the sample size. Each line was calculated for a different effect size.

For the sample size analysis we assumed a 2-tailed *t* test with significant level of 0.05. Figure 4 shows that, for medium (0.750) and large (1000–1250) effect sizes, a minimum of 30 patients per group is sufficient to control statistical variance, ensuring a test power >0.80.

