**Table 1 T1:**
[figure not shown]
Radiometric parameters.

The placebo group will be submitted to the simulation of laser application, with the device switched off; because it is an infrared and invisible length, the patient will not be able to perceive that the equipment will be turned off. In the group that receives the PBM, the device will have its timer turned off, to avoid the perception of sound difference.

The first collection of saliva will also be done in 2 steps—unstimulated and stimulated. In the non-stimulated collection, the patient will be instructed to swallow and then lower his/her head and collect in a test tube all the saliva produced during 5 minutes. The stimulated collection will be done in the same way, however, the patient will be instructed to chew a sialogogue (silicone fragment to stimulate salivary production) for 5 minutes. After the PBM sessions (4 sessions), in the following week, the saliva will be collected again in 2 steps, as in the initial collection. The initial and final volumes will be compared to verify if there was an increase in the salivary flow. A biochemical analysis will also be made.

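### The named between-group tests are valid but use baseline salivary flow inefficiently or not at all; a baseline-adjusted analysis is a free improvement

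*Protocol article*

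**What the plan says.** Section 3.3 (Statistical analyzes) is the only place where the protocol article sets out inference. After a normality check, the data are "submitted to the appropriate tests to determine the differences between the groups": a t test if the outcome looks normal, a Mann–Whitney U test if it does not. "All tests will be 2-tailed and the level of significance adopted will be" 0.05. No covariate is named, and the analysed quantity (final flow or change in flow) is not stated.

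Section 2.3 (Sample size) rests on the same kind of test, a two-tailed t "test with significant level of 0.05". It considers power "for medium (0.750) and large (1000–1250) effect sizes" and concludes that 30 per arm is enough, "ensuring a test power >0.80".

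Section 2.5 (Study interventions) has each patient give unstimulated and stimulated saliva before treatment and again afterwards. It then says: "The initial and final volumes will be compared to verify if there was an increase in the salivary flow". The Methods part of the abstract is similar: "Non-stimulated and stimulated salivary flow will be analyzed before and after the treatment". Neither sentence names a contrast between the arms.

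**The concern.** Baseline sialometry is the same measurement as the primary outcome, taken on the same patient a few weeks earlier. It is usually the best single predictor of the final value. A two-sample test of final flow leaves that information out, and any chance baseline difference between two arms of 30 stays in the estimate. A two-sample test of change uses baseline but subtracts all of it, which adds noise when the two measurements are only moderately correlated. The fallback to Mann–Whitney is unadjusted too.

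The open choice between final value and change also matters. The two can differ in power and in the estimate they give. If the choice is still open when the data are seen, it can follow the results. Finally, the sentence in section 2.5 could be taken to mean that an increase within the PBM arm counts as evidence of effect. Such an increase would not separate PBM from a response to sham or from familiarity with the collection procedure.

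**Working it through.** **Inputs from the document**
- Section 2.3: two-tailed t test, alpha 0.05, 30 per arm, standardised effect d = 0.75 as the smallest size named. The range printed as 1000–1250 is read as 1.0 to 1.25.
- Section 2.4: allocation 1:1.
- No mean or SD in mL/min is given, so SD = 1 is used with the standardised effect.

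**Assumed input**
- The baseline-final correlation ρ is not in the document. It is taken as 0.2, 0.3, 0.5 and 0.7, with equal variance at the two times.

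**Step 1: reproduce the stated power.** The noncentrality is d × √(n/2) = 0.75 × √15 = 2.905, with 58 degrees of freedom and a critical value of about 2.00. The noncentral t distribution gives power 0.815 (0.828 by the normal approximation). At d = 1.0 and 1.25 the power is 0.968 and 0.997. The claim of more than 0.80 is correct, with little margin at d = 0.75.

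**Step 2: the two readings of section 3.3 and the alternative.**
- Final values: effective effect d = 0.75, whatever ρ is.
- Change scores: effective effect d / √(2(1 − ρ)). At ρ = 0.3 this is 0.75 / √1.4 = 0.634.
- ANCOVA: effective effect d / √(1 − ρ²), with 57 degrees of freedom. At ρ = 0.3 this is 0.75 / √0.91 = 0.786.

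Power at d = 0.75 and 30 per arm:

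| Assumed ρ | t test, final value | t test, change | ANCOVA | Residual variance under ANCOVA (1 − ρ²) | Effect detectable with 80% power, ANCOVA |
|---|---|---|---|---|---|
| 0.2 | 0.815 | 0.617 | 0.830 | 0.96 | 0.721 SD |
| 0.3 | 0.815 | 0.675 | 0.849 | 0.91 | 0.702 SD |
| 0.5 | 0.815 | 0.815 | 0.909 | 0.75 | 0.637 SD |
| 0.7 | 0.815 | 0.958 | 0.979 | 0.51 | 0.525 SD |

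The detectable effect for the unadjusted final-value test is 0.736 SD.

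**Step 3: compare.** Against the final-value test, ANCOVA gains 1.5, 3.4, 9.4 and 16.4 percentage points. Against the change score, the ratio of ANCOVA variance to change-score variance is (1 − ρ²) / (2(1 − ρ)) = (1 + ρ)/2, which is below 1 for every ρ below 1. Below ρ = 0.5 the change score is weaker than the final value alone. At ρ = 0 ANCOVA still gives 0.815 to three decimals, so the lost degree of freedom costs almost nothing.

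**Step 4: illustration with losses.** Section 4 (Discussion) calls retention a barrier but gives no rate. With an assumed 10% loss (27 per arm), the final-value t test has power 0.772. ANCOVA has 0.809, 0.877 and 0.966 at ρ = 0.3, 0.5 and 0.7.

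These figures apply to the t-test branch. No calculation was made for the Mann–Whitney branch.

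**The case against.** The strongest reply is that nothing stated here is wrong. A two-sample test is valid under randomisation, the trial was sized on the same test, and the power claim reproduces. All of that stands. It can also be said that a condensed article may leave final value versus change to a fuller document. That is fair as far as the silence goes, but the article does name its tests, and under either reading they are less efficient than ANCOVA.

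Three stronger readings are tempting, and the document does not support them.
- **That the plan ignores baseline.** The sentences in section 2.5 and the abstract leave a between-group test of change possible, and that test would use baseline.
- **That the effect will be judged by a before-after test.** Section 2.5 describes why saliva is collected twice and names no paired test. Section 3.3 names only tests between groups. Regression to the mean would inflate a within-arm test if patients were selected on measured flow. However, the inclusion criteria (2.3.1) set no flow cut-off, and a randomised comparison between arms is protected from it anyway.
- **That a large gain is certain.** The coefficient of variation of about 50% in section 2.3 says nothing about the baseline-final correlation, on which the gain depends.

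**Conclusion.** The point holds as a free improvement, not as an error. The planned test is valid and its stated power is right. It makes no use of baseline if run on final values, and inefficient use if run on change.

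The size depends on an unstated correlation. At 0.2 or below the gain over the final-value test is small (0.815 to 0.830 at 0.2). From about 0.5 it is substantial (0.909 at 0.5, 0.979 at 0.7). If the intended test is on change, the case is stronger at low correlation: at 0.3 its power is 0.675, below the stated target, against 0.849 for ANCOVA. These figures assume d = 0.75, 30 analysed per arm, equal variances at the two times and a linear relation between baseline and final flow.

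**What to change.** In section 3.3, or in the analysis plan before treatment codes are opened:
- Make the primary analysis an ANCOVA of final flow on arm, with baseline flow of the same type (unstimulated or stimulated) as covariate.
- Report the adjusted PBM-minus-sham difference with its 95% CI.
- If residuals are clearly skewed, analyse log flow or use a rank-based ANCOVA, in place of the switch to an unadjusted Mann–Whitney test.
- State that the initial-versus-final comparison in section 2.5 is descriptive within each arm, and that the effect is judged only between arms.

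The cost is a few lines of wording and one degree of freedom. No extra patients, visits or measurements are needed, and the sample size stays as it is.

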It is known that neurons release ATP in the muscle, the gut and the bladder tissue as a messenger molecule. Receptors specific for ATP as for the signaling molecule (P2 family) and its final decomposition product, adenosine (P1 family), were found and identified. ATP activation of P2 receptors (P2X and P2Y subtypes) can produce different cellular effects. It seems that irradiation could be used as a replacement for growth factors. This field of research opens a new understanding of the complicated mechanisms of PBM. The role of ATP as a signaling molecule provides a new basis for explaining the versatility of the effects of phototherapy.^[23,26]^

A recent study with rats demonstrated that PBM increases the number of mitotic ducts of submandibular glands, suggesting the efficacy of PBM as a salivation stimulating agent in patients with xerostomia.^[28]^ PBM, using an infrared laser with radiant energy between 4 and 8 J per point, was shown to be effective in stimulating saliva production in rats and increased the concentration of secreted proteins in the parotid glands.

The literature lacks papers on the impact of PBM in patients with xerostomia induced by antihypertensive drugs. In the research carried out in the databases, no article was found that directed the PBM to patients with xerostomia induced by antihypertensive drugs. The great majority of the papers deal with xerostomia related to chemotherapy and radiotherapy.

The proposed treatments are only palliative, through artificial saliva, which presents an immediate result, but which presupposes several daily applications, with undesirable effects, according to reports of patients who use it.
